**Methods:**

The study will involve 140 teeth with apical periodontitis and fistulas. The teeth will be randomly assigned to one of two treatment groups. Group I will receive only the conventional endodontic treatment, which includes root canal cleaning, shaping, and obturation. Group II will undergo the same conventional endodontic treatment, but with an additional step of aPDT. The aPDT procedure involves applying a photosensitizer to the root canal and irradiating it with light to produce reactive oxygen species. Each group will consist of 70 teeth to ensure adequate statistical power. The primary outcome is fistula resolution, assessed clinically at 15 and 30 days post-treatment. The secondary outcome is the comparison of apical radiolucency from periapical radiographs to evaluate healing and reduction of periapical pathology.

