**Conclusions:**

The study aims to determine if adding aPDT significantly improves the management of apical periodontitis and overall success rates of endodontic treatment. The results will provide insights into the effectiveness of aPDT as an adjunctive treatment and its potential benefits in clinical practice.

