### Interventions

All participants will be treated by the same experienced endodontist, who will oversee both data collection and procedural management. Each participant will receive conventional treatment.

A baseline periapical radiograph will be required for all participants, as well as follow-up radiographs at 15- and 30-days post-treatment. These radiographs will be obtained by a different operator, who will analyze them. This operator will be blinded to the intervention received by each participant.

Conventional treatment will be performed using the Protaper rotary system (Dentsply Maillefer rotary instruments). The canal irrigation will be with 5% sodium hypochlorite, 17% ethylenediaminetetracetic acid, and 2% chlorhexidine [14]. Subsequently, a methylene blue solution in a surfactant medium will be applied using a size 30 paper point cone (Dentsply), with a pre-irradiation time of 1 minute. The study group will receive a 3-minute irradiation period, while the control group will be administered the photosensitizer along with a simulated laser application. This simulation will be achieved by placing an aluminum foil barrier at the tip of the laser equipment to block the light. During these procedures, both the operator and participants will wear protective eyewear to ensure eye safety and concealment. Calcium hydroxide will be applied to the root canals as a long-term intracanal dressing for endodontic treatment.

A diode laser device (Therapy EC, DMC, São Carlos, Brazil) with a wavelength of 660 nm and a power output of 100 mW will be used, according to the parameters detailed in Table 1. The pre-irradiation and irradiation durations will be identical for both groups.

**Table 1 pone.0315169.t001:** Dosimetric parameters.

PARAMETERS	
Wavelength (nm)	660
Operating mode	Continuos
Power (mW)	100
Irradiance (mW/cm^2^)	250
Target irradiated area (cm^2^)	0.4
Exposure time (s)	180
Radiant exposure (J/cm^2^)	10
Energy (J) per point	18
Number of irradiated points	2
Application technique	Entry duct and fistula
Number of sessions	1

The photosensitizer used will be methylene blue at a concentration of 0.005%, dissolved in 0.25% sodium dodecyl sulfate.

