### Randomization

Participants will be selected and randomly assigned to one of two experimental groups. Randomization will be carried out by an investigator who is not directly involved in participant treatment, using the website www.randomizer.org. The randomization results will be communicated through opaque, sealed envelopes containing information about whether the treatment is laser-based or conventional. These envelopes will be securely stored and will not be accessible to the observing researcher. Prior to treatment, the operator responsible for administering the therapy will receive the envelope to determine the assigned treatment group.

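### The Abstract says controls receive only conventional treatment, but the Interventions section gives them the photosensitizer plus sham light, so the protocol does not fix which effect the trial will report

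*Protocol article*

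**What the plan says.** The control arm is described in several places in the protocol article.

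- **Abstract, Methods.** "Group I will receive only the conventional endodontic treatment, which includes root canal cleaning, shaping, and obturation". For the other arm: "Group II will undergo the same conventional endodontic treatment, but with an additional step of aPDT". The added step is then defined with two components: "The aPDT procedure involves applying a photosensitizer to the root canal and irradiating it with light to produce reactive oxygen species".
- **Abstract, Objective and Conclusions.** The question is the value of aPDT as an addition to conventional treatment. The Conclusions put it this way: "The study aims to determine if adding aPDT significantly improves the management of apical periodontitis".
- **Introduction, final paragraph.** The aim is worded as the photodynamic effect of methylene blue in 0.25% SDS.
- **Study design.** Everyone receives conventional treatment. The study group also has aPDT, and controls have a laser simulation. Dye is not mentioned for controls here.
- **Interventions.** Methylene blue in surfactant is applied after irrigation, and "the control group will be administered the photosensitizer along with a simulated laser application". The sham consists of "placing an aluminum foil barrier at the tip of the laser equipment to block the light". The section adds: "The pre-irradiation and irradiation durations will be identical for both groups".
- **Sample size calculation.** The two arms are called the aPDT group and the sham group.
- **Randomization.** The operator opens an envelope "containing information about whether the treatment is laser-based or conventional".

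**The concern.** The word only in the Abstract and the administration of photosensitizer to controls in the Interventions section are both positive statements, and they are incompatible. This is not detail that a condensed article has left to a fuller document.

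The comparator determines what the trial can conclude. A comparison with conventional treatment alone shows what dye plus light adds. A comparison with dye plus blocked light shows what the light adds once the dye is there. If the trial runs as the Interventions section describes but is reported in the Abstract's terms, the conclusion goes beyond the data. A null result, for example, could be read as showing that aPDT adds nothing to conventional treatment, when it would show only that illumination added nothing detectable to the dye.

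The allocation wording does not settle the matter. Under the Interventions section every participant receives conventional treatment, and the laser equipment is used in both arms, so neither term in the envelope wording describes what separates the arms.

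**Working it through.** The protocol gives no figure on this point to reproduce. The check is to write out each arm and compare the contrasts.

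**Notation.** Let C be conventional treatment, P the photosensitizer (methylene blue 0.005% in 0.25% SDS), L active light and S foil-blocked light. Let R(·) be the fistula-resolution rate under a given combination.

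**Arms as described**

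| Section | Control | Experimental |
|---|---|---|
| Abstract, Methods | C | C + P + L |
| Study design | C + S (dye not mentioned) | C + aPDT |
| Interventions | C + P + S | C + P + L |
| Sample size calculation | sham group | aPDT group |
| Randomization | conventional | laser-based |

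**Contrasts**

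1. Abstract: D₁ = R(C+P+L) − R(C). This is the effect of adding aPDT as the Abstract defines it.
2. Interventions: D₂ = R(C+P+L) − R(C+P+S). This is the effect of light activation, given the dye.
3. Gap: D₁ − D₂ = R(C+P+S) − R(C). This is the effect of unlit dye and surfactant together with the sham procedure.

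So D₁ = D₂ only when unlit P with S changes nothing relative to C.

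**What the document says about the gap.** It gives no rate for C, for C + P + S or for C + P + L. The Introduction describes the photosensitizer as acting when light activates it, which is compatible with a small gap but does not measure one. The comparison of methylene blue with and without SDS cited in the Introduction was made during aPDT, so it does not describe the unlit dye.

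**Range, by assumption.** If the unlit dye and sham carried a share f of the full effect D₁, then D₂ = (1 − f) × D₁:

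- f = 0: D₂ = D₁
- f = 0.10: D₂ = 0.90 × D₁
- f = 0.25: D₂ = 0.75 × D₁
- f = 0.50: D₂ = 0.50 × D₁

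The document supports no particular value of f. The contradiction between the sections does not depend on it.

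**Which statements agree.** The aim in the Introduction matches D₂. The simulation in the Study design section and the sham label in the sample size section fit D₂ and do not fit an arm with nothing added. The outliers are the Abstract (Objective, Methods and Conclusions) and the envelope wording.

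**The case against.** The strongest reply is that the operative text is nearly consistent. The Study design section gives controls a simulation and refers to the description that follows. The Interventions section supplies that description in full, and the sample size section speaks of a sham group. A reader of the Methods knows what controls are meant to receive, the aim in the Introduction is what such a design answers, and the Abstract is a condensed text. Much of this stands. It limits the mismatch to the Abstract and the envelope wording, set against the operative Methods. It does not remove the mismatch, because nothing in the document withdraws the word only, and the Abstract is where the objective and the conclusion are put to most readers.

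Three stronger readings are tempting, and the document does not support them.

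- *The control is wrong, or the result is biased.* Dye plus sham light is a legitimate blinded control. It gives a different estimand, and randomization and the between-arm comparison remain sound for that estimand.
- *The trial loses most of its power.* That would need resolution rates under conventional treatment alone, unlit dye and full aPDT. None is given, and the sample size section states no effect size, so its 80% power cannot be tied to either contrast.
- *The operator will leave out dye and sham in controls and so unblind participants.* The Randomization section says what information the envelopes carry and does not give a verbatim label. One experienced endodontist treats everyone under a text that prescribes both for controls. Such an omission is conjecture.

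**Conclusion.** The point holds as an inconsistency in the comparator and therefore in the estimand. The Abstract and the Interventions section cannot both be right about what controls receive, and the allocation wording does not identify the sham arm. If the Interventions text governs, the trial estimates the effect of light activation in the presence of the photosensitizer. Reading that as the effect of adding aPDT to conventional treatment rests on an unstated assumption: that unlit methylene blue in SDS and the sham procedure have no effect.

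The numerical size cannot be given from the document. It is zero if that assumption is true and otherwise equals the effect of the unlit dye and sham. This should be fixed. It does not threaten the validity of the comparison if the Interventions text is followed.

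**What to change.** Reconcile the Abstract, Study design, Interventions and Randomization sections on what the control arm receives. Which comparator to use is for the investigators to decide and is not judged here.

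If the Interventions text stands:

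- Describe the control everywhere as conventional treatment + photosensitizer + sham light, including in the Abstract and the Study design section.
- State the objective and conclusion in the Abstract as the effect of light activation given the photosensitizer, in line with the aim in the Introduction.
- Word the envelopes as active light versus sham light.

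If the Abstract's comparator is the intended one, the Interventions and Study design sections, the sham label in the sample size section and the account of participant blinding must be revised to match it.

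Under the first option the cost is wording and envelope text, with a somewhat narrower claim. The Ethics and dissemination section places recruitment after acceptance for publication, so the change belongs before enrolment, or as early as possible if enrolment has begun.

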It is essential to acknowledge that the antimicrobial efficacy of antimicrobial photodynamic therapy is contingent upon the match between the absorption spectrum of the photosensitizer and the emission spectrum of the light source. The effectiveness is influenced by factors such as the wavelength of the light, irradiance, exposure duration, and the absorption characteristics of the PS [10].

The aggregation of the photosensitizer is another factor influencing the efficacy of aPDT. This phenomenon, known as dimerization, can be controlled using surfactants. Sodium dodecyl sulfate (SDS) has been demonstrated to effectively reduce this aggregation [11]. Some researchers have demonstrated that methylene blue exhibits greater antimicrobial efficacy when dissolved in ethanol or urea solutions compared to water-based solutions. The addition of surfactants, such as SDS, has been shown to mitigate MB aggregation. This results in an increased concentration of monomeric MB and a reduction in aggregate formation, due to enhanced electrostatic and hydrophobic interactions among MB molecules [9, 12].

The use of methylene blue in a SDS solution at a 0.25% resulted in more effective microbial reduction during aPDT against *Candida albicans* compared to MB alone. The study found that MB, when in its monomeric form, was a more potent photosensitizer, with Type II photochemical reactions—involving singlet oxygen—being the most effective mechanism for inactivating *C*. *albicans* [11].

Following the disruption of the biofilm during endodontic therapy, residual bacterial populations may persist within the periodontal pockets, necessitating adjunctive antimicrobial treatment. Successful endodontic treatment requires precise canal instrumentation, effective irrigation, and appropriate intracanal medication. This process encompasses both manual and mechanized techniques, the application of irrigants, intracanal medicaments, and root canal sealers, all of which involve considerable time and resources. Antimicrobial photodynamic therapy (aPDT) may serve as an adjunctive treatment modality for periodontal disease, potentially reducing reliance on systemic antimicrobials and decreasing the risk of developing bacterial resistance [9].

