## Materials and methods

### Study design

This study will be a two-arm, single-center, double-blind, randomized controlled clinical trial with a 1:1 allocation ratio. Upon approval of the study protocol by the Research Ethics Committee of the Universidad Catolica del Uruguay—UCU, the trial will be conducted involving participants with apical periodontitis and a fistula in single-rooted teeth. Inclusion criteria require initial periapical radiography demonstrating apical radiolucency and fistulography to confirm the presence of the fistula. Recruitment will occur at the University Health Clinic of UCU, where the study will be conducted. Participants will be required to read, understand, and sign the Free and Informed Consent Form, which has been approved by the Research Ethics Committee. (211103b).

All participants will receive treatment from a single experienced clinician, who will oversee data collection and procedural execution. Initial periapical radiographs will be required for all participants. Root canal preparation will be conducted using a rotary endodontic device (DENTSPLY). A diode laser apparatus (DMC, THERAPY EC, Sao Carlos, Brazil) with a wavelength of 660 nm, power output of 100 mW, and an irradiation duration of 3 minutes will be utilized [14].

Participants and outcome evaluators will remain blinded to the assigned interventions throughout the study. Unblinding will be permitted only under exceptional circumstances where knowledge of the actual treatment is critical for the ongoing management of the participants.

All participants will receive conventional treatment as described below. Additionally, the study group will undergo antimicrobial photodynamic therapy (aPDT), while the control group will receive a simulation of the laser application. During this process, both participants and the operator will be required to wear protective eyewear.

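### Table 1 gives a radiant exposure of 10 J/cm², but its other rows give 45 J/cm² per point, so the light dose per area is understated 4.5-fold

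*Protocol article*

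**What the plan says.** Table 1 in the Interventions section of the protocol article lists the laser settings. The rows that bear on dose are:

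- "Irradiance (mW/cm^2^) 250"
- "Target irradiated area (cm^2^) 0.4"
- "Exposure time (s) 180"
- "Energy (J) per point 18"
- "Radiant exposure (J/cm^2^) 10"

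The table also gives a power of 100 mW, continuous operation, two irradiated points (the canal entry and the fistula) and one session. The text refers to this table for the laser parameters.

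The Study design section repeats two of the settings: "power output of 100 mW, and an irradiation duration of 3 minutes will be utilized". The Interventions text again gives 100 mW and 3 minutes of irradiation for the study group, "while the control group will be administered the photosensitizer along with a simulated laser application".

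**The concern.** Radiant exposure is not a free setting. It follows from irradiance and time, or from energy and area, and all four of those are in the same table. The value printed does not follow from them, so no session can meet every row of the specification as written.

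The quantity is central to the intervention. Under the Interventions section both arms receive methylene blue and the control arm has its light blocked by foil, so delivered light is what the trial tests. The Introduction ties efficacy to two of the quantities whose product is radiant exposure: "The effectiveness is influenced by factors such as the wavelength of the light, irradiance, exposure duration, and the absorption characteristics of the PS". If the 10 is carried into the trial report, anyone replicating the treatment, or grouping trials by J/cm², would take the wrong dose. An operator who worked to the J/cm² row would stop far earlier than the stated 3 minutes.

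**Working it through.** **Inputs, all from Table 1:** power 0.1 W; area 0.4 cm²; irradiance 0.250 W/cm²; time 180 s; energy 18 J per point; two points; continuous mode, so there is no duty-cycle reduction. Power and time are confirmed in the Study design and Interventions text.

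**Rows that reproduce**

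- Irradiance = power / area = 0.1 / 0.4 = 0.250 W/cm² = 250 mW/cm², as stated.
- Energy per point = power × time = 0.1 × 180 = 18 J, as stated.

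**Row that does not reproduce**

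- Radiant exposure = irradiance × time = 0.250 × 180 = 45 J/cm².
- Radiant exposure = energy / area = 18 / 0.4 = 45 J/cm².
- Stated: 10 J/cm². Ratio 45 / 10 = 4.5.

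**Other readings that might have given 10**

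- 180 s shared between the two points (90 s each): 0.250 × 90 = 22.5 J/cm². Energy would also be 0.1 × 90 = 9 J per point, against the stated 18 J.
- Both points summed over both areas: 36 J / 0.8 cm² = 45 J/cm².
- Both points summed over one area: 36 J / 0.4 cm² = 90 J/cm².

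None gives 10.

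**What would have to change to keep 10 J/cm²**

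| Entry changed | New value | Other entries that must then change |
|---|---|---|
| Time | 10 / 0.250 = 40 s | Energy to 0.1 × 40 = 4 J; the 3-minute statements in the text |
| Area | 18 / 10 = 1.8 cm² | Irradiance to 100 / 1.8 = 55.6 mW/cm² |
| Power | (10 / 180) × 0.4 = 0.0222 W = 22.2 mW | Irradiance to 55.6 mW/cm²; energy to 0.0222 × 180 = 4 J; the 100 mW statements in the text |

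Each of these needs at least two entries altered. Changing the radiant exposure row from 10 to 45 needs one.

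**The case against.** The best counter-argument is that the settings an operator actually controls are consistent. Power is 100 mW and time is 3 minutes wherever they appear, and mode, points and sessions are clear. If those are followed, each point receives 18 J whatever the radiant exposure row says, and a careful reader can recompute 45. On this view the fault is one derived cell with consequences for reporting only. That stands as a limit on the consequences: it is why the point does not reach the trial's inference. It does not make the row right, because the text makes the table the specification for the laser and dose per area is one of the figures by which the treatment will be described.

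Three narrower points also have some force.

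- Only the dose per area is wrong. The energy of 18 J per point is correct.
- The sentence from the Introduction names irradiance and duration, not radiant exposure, and those two rows agree with the rest of the table. Its support is therefore indirect.
- The Abstract describes Group I as having conventional treatment alone and places the photosensitizer in the Group II step. The statement that light is the only planned difference therefore rests on the Interventions section. The arithmetic does not depend on it.

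**Conclusion.** The concern holds. Table 1 understates the radiant exposure 4.5-fold: 10 J/cm² stated, against 45 J/cm² per point from its own rows. This needs no outside figure, only the identities linking power, area, time and energy.

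Which entry is wrong is a judgement. The 10 is the likely error, because power and time are repeated in the text and five rows agree without it. The document cannot exclude that 10 J/cm² was the intended target. In that case time and energy are 4.5 times too high: 180 against 40 s and 18 against 4 J per point, or 360 against 80 s and 36 against 8 J over two points. Nothing in the article mentions 40 s or 4 J.

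The error concerns how the intervention is specified and reported. It should be fixed, but it does not touch sample size, type I error, blinding or the comparison between arms.

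**What to change.** Have the sponsor confirm the intended dose and, before the first participant is treated, correct the radiant exposure row to 45 J/cm² per point.

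If 10 J/cm² is what was meant, leave that row, change time and energy to 40 s and 4 J per point, and amend the 3-minute statements in Study design and Interventions.

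A minor clarification at the same time would be to say that the 180 s applies to each point, so that two points take 2 × 180 = 360 s and 2 × 18 = 36 J. The energy row already implies this, but the text speaks of a single 3-minute period. The article already keeps irradiation times equal between arms, so the sham needs no separate wording beyond following the same per-point time.

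If recruitment has begun, the correction is still needed for the trial report, together with a statement of the time per point actually used.

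The cost is one table cell and two words, with no added participants or procedures. The less likely alternative means two cells and the matching text.

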### Inclusion criteria

A single root tooth with apical periodontitis and fistula; periodontal pockets ≤ 4 mm; ≥ 18 years of age and not taking antibiotics.

